# METHODOLOGY

## Study diagram

We propose a single-center pilot study to characterize the acceptability and usability of the beta version of the eMind application among smokers. The effect size of this intervention on the maintenance of smoking abstinence will be collected as a secondary endpoint.

## Calculating the number of subjects required

### **Justification**

We will include 60 patients (N = 60). The number is based on the sample size commonly used in pilot studies. In addition, we are planning three different focus groups with 6 to 8 participants in each. Given the potential for some participants to be lost to follow-up and unavailable to participate in focus groups, N = 60 seems to us to fit in well with the chosen methodology

### **Feasibility**

The project leader is an addictology doctor trained in Mindfulness and practicing in an addictology department with extensive experience in clinical research in tobacco (recruitment of 117 participants over 24 months for the Tabacstim 2 and 3 projects).

## Study population

### **Inclusion criteria**

- Person having given oral consent

- Adults aged 18 and over

- Smoker with a DSM-5 smoking disorder

- With motivation to quit smoking

- With daily access to a smartphone

- Able to understand written and spoken French

### **Non-inclusion criteria**

- Person under legal protection (curatorship, guardianship)

- Person subject to a safeguard of justice measure

- People with cognitive disorders that prevent training.

- Currently using other smoking cessation treatments (burpropion, varenicline), apart from NRT.

- Suffering from an acute psychiatric or somatic disorder requiring hospitalization / not stabilized

- With a contraindication to replacement therapy

- Have an alcohol use disorder or consume illicit products

- Pregnant, parturient, breastfeeding or planning to become pregnant within the next 6 months

- Person not affiliated to the national health insurance scheme

## Project feasibility

We expect a high level of feasibility for our intervention, as it will be of light intensity, favoring participant compliance. In addition, a large number of smokers in the general population will enable our recruitment. In our trial, participants will be recruited by healthcare professionals, which favours the suitability of the intervention for each participant.

This research is being carried out as part of the activities of the Addictology Department at Dijon University Hospital. This department is a level 3 facility, which positions the hospital as a regional referral center in the field of addictions. It offers a comprehensive range of care services, combined with the research and teaching missions of a hospital such as Dijon Bourgogne University Hospital. The Addictology Department at Dijon University Hospital has a specialized tobacco consultation. This is by addictology physicians and nurses qualified in the field. An active file of smokers intending to stop smoking is clearly identified among the patients consulting the service (smoking = 30% of consultants). In addition, the department has extensive experience in clinical studies on tobacco.

The inclusion period will last 21 months. Follow-up will last 6 months. The study will therefore last 27 months.

# INTERVENTION

## Study intervention

The study consists of the following two phases:

1. Supported learning phase (8 weeks) :

This phase will consist of Mindfulness training via the beta version of the eMind smartphone application, in addition to the standard treatment (TSN). The eMind application contains 8 thematic modules linked to both Mindfulness training and tobacco consumption (one module per week). Tools for daily practice will be available in audio/video and text formats (PDF documents). For each module, key messages will be delivered through a weekly video, and Mindfulness sessions ranging from 5 to 15 minutes each, available for daily practice (body scan, movement, breathing, etc.). The modules will target specific elements of addiction such as craving and automatic behavior, as well as transdiagnostic elements such as emotion, self-judgment and acceptance.

During this phase, each week a new module will be made available to the participant. Previously delivered modules will remain available for consultation at the patient's convenience.

*Summary of topics covered by the 8 learning modules :*

- Week 1: Introduction to Mindfulness
- Week 2: Addiction and automatic behavior
- Week 3: Craving
- Week 4: Emotion
- Week 5: Shame and judgment
- Week 6: Acceptance
- Week 7: Relapse
- Week 8: Building your practice

1. Independent practice phase :

The eMind application is designed to help participants acquire the skills they need to practice Mindfulness independently. Therefore, after the 8-week learning period, no new modules will be made available to participants. However, participants will be able to access all eMind resources as part of their autonomous practice

The smoking schedule (0 = no smoking, 1 = 1 cigarette, etc.; daily fill-in) and a craving assessment tool (VAS between 0 and 10; weekly fill-in) will also be implemented in the application. Similarly, the mindfulness practice calendar will be collected via the app (Do you practice mindfulness today: YES/NO, daily fill-in). In the event of non-completion of the calendar or the craving VAS, the principal investigator will receive alerts and will be able to contact the participant to offer help in the event of difficulties.

Through the eMIND application, two other types of alert will be set up:

- Patient reminders if video content is not viewed
- Alerts on the clinician interface in the event of non-viewing of video content by the patient.

## Associated treatments

Participants in this study will receive NRT in transdermal (patch) and oral (lozenge) forms, which is a standard treatment in this indication. The evolution of NRT doses will depend on the patient's clinical assessment, thus reproducing real NRT treatment conditions. The nicotine patch is applied to dry skin every 24 hours. Lozenges will be used as needed, up to 10 lozenges per day.

# COURSE OF THE STUDY

## Recruitment procedures

Eligible patients are identified prospectively by an investigating physician. These are generally patients seen as part of a psychiatric or addictology consultation at their own request, or referred by a general practitioner, or as part of a psychiatric or addictology liaison at the CHU

## Information and free and informed consent , screening methods

If the patient meets the eligibility criteria, the investigating physician will present the study during a tobaccology consultation in the Addictology Department of the CHU Dijon Bourgogne. He will inform the patient of the nature of the research, its objectives, methodology, duration, expected benefits, constraints and foreseeable risks, in accordance with article L1122-1 of the CSP. The investigating physician will give the patient the information note. Patients will be free to ask any questions they may have about the research, will be allowed a period of reflection and will be informed of their right to refuse to take part in the research or to withdraw their consent at any time without prejudice and without having to justify the reasons for their decision.

If the patient agrees, oral, free and informed consent will be obtained from one of the physician-investigators. The participant will be free to ask any questions about the research, and will be given a period of time reflect on his or her decision. If the patient agrees, his or her oral, free and informed consent will be obtained by one of the physician-investigators. A copy of the information note will be given to the patient, and two copies of the attestation d'obtention de consentement oral (ACOP) will be completed by the physician-investigator and kept by the patient and the investigator respectively. The investigator must record in each patient's medical file the fact that the patient has been informed and is included in a research protocol.

## Inclusion criteria

During the inclusion visit (Visit 1), the inclusion and non-inclusion criteria will be verified, oral informed consent will be obtained from the investigating physician, tobacco consumption over the last 28 days will be assessed, exhaled CO will be measured, and craving intensity will be assessed using a visual analog scale (VAS). During this visit, the eMind application will be presented and the participant will be given an access code to download it. The first connection to the application will be made with the investigator, in order to enter the inclusion number, which cannot be changed afterwards. Following this visit, participants will begin their MBI practice using the application associated with nicotine replacement therapy.

The investigator will collect socio-demographic information (age, sex, professions and socio-professional categories, urban/rural residence), medical and surgical history, usual treatments, as well as tobacco consultation data.

Inclusion visits will be grouped into 3 waves of 20 patients, to enable focus groups to be set up and conducted from week 9 onwards.

## Follow-up / questionnaires

Participants will receive follow-up visits at 4 and 8 weeks of inclusion, as follows:

- Visit 2 (4 weeks from inclusion, university hospital addictology department at CHU Dijon Bourgogne)

- Collection of consumption schedule, measurement of CO

- Assessment of craving using VAS

- Assessment of withdrawal symptoms and NRT use

- Gather initial feedback on the regularity of use of the application in order to plan the formation of focus groups.

- Visit 3 (8 weeks from inclusion, University Hospital Addictology Department, CHU Dijon Bourgogne)

- Collection of consumption schedule, measurement of CO

- Assessment of craving using VAS

- Assessment of withdrawal symptoms and NRT use

- Assessment of eMind usability using the MARS scale

- Collect feedback on the regularity of application use.

The focus groups will be carried out between visit 3 and visit 4, in order to avoid any memory bias that might arise if they are carried out too far after the product has been used.

In order to obtain an overall assessment of feedback, expectations and the determinants of the application's acceptability and impact on participants, the following topics will be addressed during the focus groups:

- Knowledge/representations of eHealth tools: history, practice in what context, general opinion of eHealth tools

- Practical application and access to the tool: access to the tool (connection, handling, navigation, etc.), general appearance, flexibility and adaptability of use, suitability of the tool to the smoking cessation context

- Perceived impact on smoking behavior: changes in smoking habits, obstacles, helping factors, shortcomings.

- Improvements to the tool and addictology follow-up: additions/improvements to the tool/follow-up visits, application reminders, online tools for self-monitoring of consumption, access to healthcare professionals.

Visit 4 to 12 weeks after inclusion (M3). During this visit, the following tests will be performed:

- Collection of consumption schedule, measurement of CO

- Assessment of craving using VAS

- Assessment of withdrawal symptoms and NRT use

## End of study

Telephone call 6 months after inclusion, during which the following information will be collected:

- Tobacco consumption at 6 months
- A compendium of mindfulness practice

## Feedback session

Once the results have been analyzed and the modifications made in line with the participants' feedback, we will propose a feedback session to present the results of the study and the new version of eMind.

##

## Technical description of measured parameters

- Tobacco consumption calendar, rated 0 = no consumption, 1 = 1 cigarette, etc., integrated into the eMind application: daily completion by the patient (with reminder notification).
- EVA Visual Analog Scale ("craving") rated from 1 to 10, integrated into the eMind application: weekly completion by the patient (with reminder notification).
- MARS-F Mobile Application Evaluation Scale composed of 23 items scored from 1 to 5 and exploring four objective domains (engagement, functionality, aesthetics, information quality) leading to a score between 0 and 95 and a 20-point subjective domain: collected at each visit by the investigator [15].
- Mindfulness practice calendar, integrated into the eMind application: daily completion by the patient (with reminder notification).

## Benefit-risk balance

On an individual level, the practice of mindfulness, through learning the key messages of the 8-week MBI program, could lead to better tolerance of craving and a lower risk of relapse after smoking cessation.

On a collective level, the practice of mindfulness using eMind could be an important addition to standard care, extending access to mindfulness to as many patients as possible.

MBIs have been extensively studied in various clinical trials in the fields of mental health, addiction, pain and stress management. Literature data suggest that MBIs are well tolerated, provided that contraindications (any acute psychic or somatic condition) are respected.

Foreseeable side effects include those associated with smoking cessation (cravings, difficulty concentrating, headaches, irritability, fatigue, hunger, constipation) and the use of nicotine replacement therapy (skin irritation, abdominal pain, hiccups, gastroesophageal reflux, sleep disorders, nausea, diarrhea, dizziness).

We expect the application to be well accepted and used throughout the treatment period. Knowledge of the acceptability and use of the eMind tool, as well as a study of the motivations and obstacles to its use, will help us to make the necessary adjustments before rolling out the program on a larger scale.

## Description of the rules for discontinuing a person's participation in research

All those included will be followed until the end of the study, except for patients who have withdrawn their consent.

## Exclusivity - exclusion period

| Exclusivity period  If yes, the patient cannot participate simultaneously in another research project | yes  no |
| --- | --- |
| Exclusion period  If yes, the patient may not participate in other research at the end of this one for a defined period of time. | yes  Duration: ....  no |
| Amount of compensation received by a patient for taking part in a focus group | 30€ |

## Study schedule

### **Study duration**

| Inclusion time | 21 months |
| --- | --- |
| Follow-up time for one person | 6 months |
| Total study duration  (from 1st inclusion to last patient follow-up) | 27 months |

### **Study organization chart**

|  | Screening | Visit 1  Inclusion | Visit 2  S4 | Visit 3  S8 | Visit 4  S12 | Phone call  M6  (End) |
| --- | --- | --- | --- | --- | --- | --- |
|  | J-x | J0 |  |  |  |  |
| Informed consent | X | X |  |  |  |  |
| Clinical examination | X | X |  |  |  |  |
| Patient questionnaires |  | X | X | X | X |  |
| CO test |  | X | X | X | X |  |
| Withdrawal-related symptoms |  |  | X | X | X |  |
| Dispensing treatment |  | X | X | X | X |  |
| Tobacco consumption |  | X | X | X | X | X |
| Mindfulness practice |  | X | X | X | X | X |

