| Course of the study | - Chronological description of the study  1. Screening visit (university hospital addictology department at CHU Dijon Bourgogne)   - Informing the person wishing to participate in the research. Oral, free and informed consent  - Checking inclusion and non-inclusion criteria   1. Visit 1 (Inclusion, University Hospital Addictology Department, CHU Dijon Bourgogne). Inclusion visits will be grouped into 3 waves of 20 patients to enable focus groups to be set up and conducted from week 9 onwards.   - Checking inclusion and non-inclusion criteria  - Oral, free and informed consent collected by visit 1 at the latest.  - Collection of tobacco consumption over the last 4 weeks, measurement of CO  - Assessment of craving using VAS  - Presentation of the application, explanation of how it works and recommendations for use, decision on associated nicotine replacement therapy.  - After the visit, introduction to Mindfulness practice using the eMind application.   1. Visit 2 (4 weeks from inclusion, university hospital addictology department at CHU Dijon Bourgogne   - Collection consumption schedule, measurement of CO  - Assessment of craving using VAS  - Assessment of withdrawal symptoms and NRT use.  - Gather initial feedback on regular use of the application to plan focus groups   1. Visit 3 (8 weeks from inclusion, University Hospital Addictology Department, CHU Dijon Bourgogne   consumption schedules, measuring CO  - Assessment of craving using VAS  - Assessment of withdrawal symptoms and NRT use - Assessment of eMind usability using the MARS scale  - Gathering feedback on regular use of the application  The focus groups will be carried out between visit 3 and visit 4, to avoid any memory bias that might arise if they are carried out at too great a distance from use   1. Visit 4 (12 weeks from inclusion, University Hospital Addictology Department, CHU Dijon Bourgogne   - Collection consumption schedule, measurement of CO  - Assessment of craving using VAS  - Assessment of adverse effects   1. Telephone call 6 months after inclusion   - Tobacco consumption at 6 months  - A compendium of mindfulness practice |

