## Secondary objectives

Study changes in tobacco consumption between inclusion and last follow-up (6 months).

Study the impact of eMind on smoking at 3 and 6 months after inclusion.

Study the evolution of craving between inclusion and the last visit (12 weeks).

Evaluate the tolerance of smoking cessation supported by the eMind application.

Study the evolution of mindfulness practice at 3 and 6 months.

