## Secondary endpoints s

The evolution of tobacco consumption between inclusion and 4 weeks, 8 weeks and 12 weeks will be measured using an electronic consumption calendar implemented in our application. A CO test will be performed at inclusion, 4 weeks, 8 weeks and 12 weeks. Smoking abstinence will be defined as the absence of tobacco consumption for 7 days prior to the assessment visit. A recent consensus of experts has recommended the use of 7-day punctual abstinence as an endpoint, as it is less affected by recall bias and missing data than continuous abstinence (16).

Assessment of tobacco consumption at 6 months, during a telephone call.

Craving intensity will be measured at baseline, 4 weeks, 8 weeks and 12 weeks using a visual analog scale (VAS) implemented in the application.

The evolution of mindfulness practice between inclusion and 4 weeks, 8 weeks, 12 weeks will be measured using an electronic consumption calendar implemented in our application.

Evaluation of mindfulness practice at 6 months, during a telephone call.

Symptoms related to smoking cessation (cravings, difficulty concentrating, headaches, irritability, fatigue, hunger, constipation), use of nicotine replacement therapy (skin irritation, abdominal pain, hiccups, gastroesophageal reflux, sleep disorders, nausea, diarrhea, dizziness) or MBI will be collected throughout the study.

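### Apart from the craving VAS, the tolerance endpoint has no structured Visit 1 baseline, and its stated collection period does not match the schedule

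*Protocol*

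**What the plan says.** Section 2.2 of the protocol sets this secondary objective: "Evaluate the tolerance of smoking cessation supported by the eMind application". Section 3.2 gives the endpoint. It lists seven symptoms of cessation and eight of NRT, and ends by saying that symptoms related to these "or MBI will be collected throughout the study". The synopsis repeats this. Section 6.11.1 gives 6 months of follow-up per person.

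The organization chart in section 6.11.2 has one symptom row, "Withdrawal-related symptoms". It is marked at Visits 2, 3 and 4 (weeks 4, 8 and 12) and is blank at screening, at Visit 1 and at the 6-month call.

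Section 6.4 schedules "Assessment of withdrawal symptoms and NRT use" at Visits 2, 3 and 4. For Visit 4 the synopsis has "Assessment of adverse effects" instead. The study diagram adds an AR collection at Visit 2 and an EI collection at Visits 3 and 4; the abbreviation list defines EI as undesirable effects. Section 6.5 limits the 6-month call to tobacco consumption and "A compendium of mindfulness practice".

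**The concern.** In a single-arm study, the participant's own state before the intervention is the only comparator for tolerance. Several listed symptoms (headaches, fatigue, irritability, difficulty concentrating, reflux, sleep disorders) are non-specific and can be present before anyone stops smoking. The non-inclusion criteria (section 4.3.2) exclude users of other cessation drugs but make an exception for NRT, so NRT-type symptoms may also be present at entry.

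If the symptoms are first recorded at week 4, a complaint noted then may be new, worse, unchanged or improved, and the data will not reliably show which. This is a gap in data collection, so a statistical analysis plan cannot close it afterwards.

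Two further points are separate from the baseline question. The endpoint promises collection over the whole study, while the schedule stops at week 12. And MBI effects, which belong to the intervention under study, are the least specified part of the endpoint.

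**Working it through.** The protocol states no figure for this endpoint, so there is nothing to reproduce. The check sets the endpoint text beside each statement of what is collected and when.

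**1. Timing of symptom collection**

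| Time point | Structured symptom collection scheduled | Source in the protocol |
| --- | --- | --- |
| Visit 1 | Craving VAS only | Synopsis, 6.3, 6.11.2 |
| Visit 2, week 4 | Withdrawal symptoms and NRT use; AR collection | 6.4, 6.11.2; diagram |
| Visit 3, week 8 | Withdrawal symptoms and NRT use; EI collection | 6.4, 6.11.2; diagram |
| Visit 4, week 12 | Withdrawal symptoms and NRT use (6.4); adverse effects (synopsis); EI collection (diagram) | 6.4, 6.11.2; synopsis; diagram |
| 6-month call | None | Synopsis, 6.5, 6.11.2 |

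Taking 6 months as 26 weeks, 26 − 12 = 14 weeks of participation follow the last scheduled symptom assessment.

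**2. Items with a baseline**

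Section 3.2 lists 7 + 8 = 15 symptoms. Craving is measured by VAS at Visit 1. That leaves 15 − 1 = 14 symptoms with no scheduled structured measurement at Visit 1.

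**3. Whether another Visit 1 entry fills the gap**

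- Section 6.3 records medical and surgical history, usual treatments and tobacco consultation data. These may mention a complaint, but they are not the same questions asked the same way at later visits.
- The chart marks a clinical examination at screening and Visit 1. No symptom list is attached to it.
- The chart marks patient questionnaires at Visits 1 to 4. The measured parameters in section 6.7 are the consumption calendar, the craving VAS, the MARS-F and the practice calendar. Of these, only the craving VAS measures a symptom.

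**4. MBI effects**

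Section 3.2 and the synopsis name them as collected. Unlike cessation and NRT, they have no listed symptoms. They do not appear in the section 6.4 visit lists or in the chart's row label. The general adverse-effect entries in the synopsis and the diagram could capture them, but section 6.4 does not carry those entries over.

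**5. Scale, as illustration only**

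Suppose a share p of the 60 participants has a given symptom at entry, it persists to week 4 and nobody is lost. Then 60 × p participants report it without its being new:

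- p = 0.10: 60 × 0.10 = 6
- p = 0.20: 60 × 0.20 = 12
- p = 0.40: 60 × 0.40 = 24

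The values of p are assumed. Losses to follow-up, which section 4.2.1 anticipates, and symptoms that resolve would both lower these counts.

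**The case against.** The strongest case on the other side is that this is a descriptive pilot in minimal-risk research. Its primary objective is acceptability and usability, no test is planned (section 10.3), no tolerance threshold is set, and safety follows standard care (section 9). Visit 1 is not empty either: it has craving, history and, in the chart, a clinical examination. All of that stands. It limits the weight of the point but does not supply a like-for-like baseline for the other 14 symptoms.

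A reader might go further than the documents allow in four ways:

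- **That existing complaints will be counted as effects of cessation, NRT or the app.** The protocol does not say so. The endpoint speaks of symptoms related to these causes, which implies some judgement, and no attribution rule is stated. What can be said is that existing and new complaints cannot be reliably separated.
- **That the app's own tolerability is not captured at all.** Section 3.2 names MBI symptoms, and the synopsis and diagram plan general adverse-effect collection. The defect is that MBI effects are not itemised or carried through to section 6.4 and the chart.
- **That the 6-month gap adds to the misattribution.** It does not. It is a separate mismatch between the endpoint's wording and the schedule.
- **That 6 to 24 participants will be misclassified.** Those counts rest wholly on an assumed prevalence and on persistence of the symptom.

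It is also fair to object that a baseline free of NRT cannot be had for people already using it at entry. The fix therefore asks only that current use be recorded.

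**Conclusion.** The point holds as a gap in data collection for a secondary endpoint, together with inconsistencies in wording. As scheduled, 14 of the 15 listed symptoms have no structured Visit 1 value, so the study cannot reliably distinguish new or worsened symptoms from existing ones. The promise of collection over the whole study conflicts with a schedule that ends symptom assessment at week 12 of a 6-month participation. MBI effects are named but not operationalised, and the Visit 4 wording differs between the synopsis and section 6.4.

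The size of the effect on reported tolerance rates cannot be derived from the protocol, which gives no baseline rates. The conclusion assumes that the visit lists and chart describe what will actually be done, and that no symptom checklist is contained in the Visit 1 patient questionnaires; none is described. The primary objective is unaffected. The change should nevertheless be made, because a missed baseline cannot be recovered by later analysis.

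**What to change.** - Complete the same symptom checklist at Visit 1, before the first app session, and again at Visits 2, 3 and 4. At Visit 1, record whether NRT is already in use.
- Include an item or an open question for effects that the participant attributes to mindfulness practice, and carry it into section 6.4 and the chart.
- Report symptoms that are new or worsened relative to Visit 1, beside the raw frequencies.
- Reconcile section 3.2 and the synopsis with the schedule: either add symptoms to the 6-month call or limit the endpoint to 12 weeks.
- Use the same Visit 4 wording in the synopsis, section 6.4 and the study diagram.

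The cost is a few minutes at a visit that already takes place, one e-CRF page and a revised chart row. If the 6-month option is chosen, the existing call becomes slightly longer. No extra visit is needed.
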